## Abstract

**Background:**

Sacroiliac joint (SIJ) dysfunction is associated with significant pain, disability, and altered postural control in adults. Manual therapies, including Mulligan mobilization, Maitland mobilization, high-velocity thrust (HVT), and muscle energy technique (MET), are routinely applied for the management of SIJ dysfunction. However, comparative evidence regarding their effects on pain, disability, and center-of-gravity (COG) displacement remains insufficient.

**Objective:**

This study aims to compare the efficacy of Mulligan mobilization, Maitland mobilization, HVT, and MET in improving pain, functional disability, and COG displacement in individuals with SIJ dysfunction.

**Methods:**

A randomized controlled, parallel-group trial will be conducted on participants diagnosed with unilateral SIJ dysfunction. Participants will be assigned in equal numbers to 4 groups, each receiving Mulligan mobilization, Maitland mobilization, HVT, or MET interventions administered 5 days per week for 3 weeks, in addition to a standardized exercise regimen. The primary outcomes will be pain (assessed using a visual analog scale [VAS]) and functional disability (assessed using the Modified Oswestry Disability Index [MODI]), and the secondary outcome will be COG displacement (measured by sway velocity, lift-up index on the left and right, COG alignment, movement time, and impact index).

**Results:**

We hypothesize that all interventions will lead to statistically significant reductions in pain and disability. Results will be analyzed after the completion of the study.

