Although each technique is well established individually, no comparative study has been conducted to evaluate the relative efficacy of these manual therapy approaches. A comparative analysis of these techniques could provide valuable evidence to guide clinical decision-making and optimize treatment outcomes for individuals with SIJ dysfunction.

This study aims to compare the efficacy of Mulligan mobilization, Maitland mobilization, HVT, and muscle energy technique (MET) in improving pain, functional disability, and COG displacement in patients with SIJ dysfunction and to rank these approaches according to their efficacy.

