### Study Design

This is a prospective, 4-arm, parallel-group, randomized controlled trial to assess superiority. The study protocol was developed in accordance with the SPIRIT (Standard Protocol Items: Recommendations for Interventional Trials) guidelines. Data will be collected on pain, disability, and COG displacement. The trial will be reported in accordance with the CONSORT (Consolidated Standards of Reporting Trials) 2010 guidelines.

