### Intervention

This study is designed to evaluate the therapeutic impact of different intervention protocols in patients with SIJ dysfunction. The study will include 4 intervention groups, each receiving conventional moist heat therapy, a manual therapy technique specific to each group, and lumbar stabilization exercises. Treatment sessions for all groups are designed to optimize outcomes and will occur 5 days per week for 3 weeks.

At the start of each session, participants in all groups will receive an identical moist heat treatment via commercial hot packs placed directly against the back for 10 minutes. Then, participants will receive the assigned manual therapy. Group A will receive Mulligan mobilization [9] to the sacral region, focusing on correcting SIJ alignment. Two distinct approaches will be used based on established protocols. These mobilizations will be delivered in 3 sets of 10 repetitions, with a 1-minute rest between sets. Group B will receive Maitland mobilization [8] in 3 sets of 30 seconds each. For the first 2 weeks, group B participants will receive grade 1 to grade 2 Maitland mobilization, and in the third week, grade 3 Maitland mobilization will be given. Group C will receive HVT [10,11], including anterior and posterior thrusts targeting the ilium, administered with the participant positioned supine or in a side-lying position. Specific maneuvers will also be used to correct up-slip and down-slip of the ilium using rapid, controlled thrusts applied by the clinician to restore joint alignment. Group D will receive MET [12,13] to correct anterior SIJ dysfunction, with the participant lying in a lateral position on the unaffected side with the affected leg flexed to the point of initial tension. A contraction intensity of 20% will be used.

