### Data Analysis

Statistical analyses will be carried out using SPSS software (version 25.0; IBM Corp). To determine the significance of the differences between the 4 groups, we will first establish normality and then choose which test to use based on the distribution of the data. We will use mixed-design ANOVA if the data are normally distributed and the Friedman test if the data are not normally distributed. Statistical analysis will use a linear mixed-effects model for group-by-time interaction. Analyses will follow the intention-to-treat principle. Missing data will be handled by the missing-at-random assumption using maximum likelihood estimation. Planned pairwise comparisons will be adjusted for multiple testing using the Holm method. Repeated-measures ANOVA will be used to determine the significance of changes among the baseline, postintervention, and follow-up assessments. Frequency distribution and descriptive statistics will be used to analyze demographic information. For all statistical tests, *P*<.05 will be considered statistically significant, and 95% CIs will be reported.

Data collection and reporting will be performed under the guidance of the principal investigators, and documentation for the analysis will be reviewed for accuracy. An Excel spreadsheet containing the study data will be provided to a statistician who will be blinded to treatment allocation for statistical analysis after study completion. The trial data will be stored in a secure, locked location for later analysis by a biostatistician and the primary researcher (NC).

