## Discussion

### Primary Findings

We hypothesize that all 4 groups will experience significant reductions in both pain and functional disability. It is expected that COG alignment will also improve after the intervention. The interventions in this study will target distinct pathophysiological elements of SIJ-related complaints. Altered arthrokinematics is a leading cause of SIJ dysfunction, which mobilization may target; mechanical restriction and compensatory motor patterns may also be addressed.

The 4 manual therapy methods have different mechanisms, but reduction in VAS scores is anticipated in all groups. This hypothesis differs from the findings of Trager et al [18], who concluded in a systematic review that manual therapy did not significantly reduce pain. Mulligan mobilization helps to relieve pain linked with bone alignment abnormalities [19] and works on the principle of sustained accessory glide with active movement, which helps to restore pain-free joint tracking. This approach may be used to address postural control and asymmetric intra-articular translation [20,21]. Maitland mobilization is an oscillatory graded mobilization, which helps to reduce hypomobility and irritability of the SIJ [22] along with associated pain and disability. HVT induces cavitation-mediated neurophysiological responses and proprioceptive input from the SIJ, and it facilitates kinematic adjustments [23-25]. MET involves voluntary isometric contractions followed by stretching and uses postisometric relaxation and autogenic inhibition to lengthen hypertonic musculature surrounding the SIJ [26,27]. The assessment of pain, functional disability, and COG displacement is important in SIJ rehabilitation, as dysfunction leads to functional limitations and impairment. Furthermore, COG displacement is linked with altered neuromuscular control and postural stability, and changes in COG alignment are linked with long-term disability. We hypothesize that 3 weeks of treatment in all 4 groups will reduce COG displacement but will not completely return the COG to a neutral alignment.

Although some participants may have muscular abnormalities or imbalance associated with SIJ dysfunction, these factors will not be targeted by in this intervention. Future studies could investigate the long-term effects of the manual therapy techniques in this study and compare them with other manual therapy techniques.

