### Conclusions

This 4-arm, parallel-group randomized controlled trial will establish the comparative efficacy of 4 manual therapy techniques—Mulligan mobilization, Maitland mobilization, HVT, and MET—in patients with SIJ dysfunction. Pain, functional disability, and COG displacement will be assessed as outcomes. The comparative effects of the interventions will be evaluated based on statistical analysis after completion of the intervention and follow-up. We hypothesize that all groups will demonstrate significant reductions in pain, functional disability, and COG displacement.

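### Every stated hypothesis is a fall from baseline within all four arms, which does not match the superiority and ranking aim and is not tied to the between-arm tests the protocol plans

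*Protocol article*

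**What the plan says.** **The aim.** Study Design calls the study a "randomized controlled trial to assess superiority". The Objective is to compare the efficacy of the four techniques, and the Introduction adds the intention "to rank these approaches according to their efficacy".

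**The hypothesis.** It is stated in three places:
- Abstract, Results: "We hypothesize that all interventions will lead to statistically significant reductions in pain and disability".
- Discussion, Primary Findings: "We hypothesize that all 4 groups will experience significant reductions in both pain and functional disability".
- Discussion, Conclusions: "We hypothesize that all groups will demonstrate significant reductions in pain, functional disability, and COG displacement".

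**The analyses.** For change over time, Data Analysis says "Repeated-measures ANOVA will be used to determine the significance of changes among the baseline, postintervention, and follow-up assessments". The same section also plans a linear mixed-effects model for the group-by-time interaction, intention-to-treat analysis and Holm-adjusted pairwise comparisons. Outcomes says that changes will be compared among the four groups after the 2-month follow-up, which is the primary end point for pain and disability.

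**The arms.** Intervention describes four groups, "each receiving conventional moist heat therapy, a manual therapy technique specific to each group, and lumbar stabilization exercises". The exercise is done in the clinic and twice daily at home. Eligibility Criteria requires symptoms of 4 to 8 weeks' duration.

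**The concern.** The hypothesis and the aim ask different questions. A superiority or ranking aim concerns differences between randomised arms. The stated hypothesis concerns each arm's own fall from baseline, a comparison that randomisation does not protect.

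Here a fall from baseline is a mixture. Natural course in people with recent symptoms, regression to the mean in people presenting for care, heat, exercise and the manual technique all contribute. No arm omits the technique, so nothing in the design separates its share from the rest.

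At stake is what the final paper may claim. If the hypothesis stands, four significant falls count as its confirmation and invite the conclusion that all four techniques work. The Discussion already leans this way: it sets the expected pain reduction in all groups against a systematic review that concluded that manual therapy did not significantly reduce pain. Meanwhile the question that randomisation can answer has planned tests but no stated hypothesis.

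**Working it through.** **1. Side by side.**

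| Element | What is compared | Where |
|---|---|---|
| Aim: superiority, ranking | between arms | Study Design; Introduction |
| Hypothesis, stated three times | each arm with its own baseline | Abstract; Primary Findings; Conclusions |
| Repeated-measures ANOVA | time points | Data Analysis |
| Comparison of changes, group-by-time model, Holm pairs | between arms | Outcomes; Data Analysis |

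The first and last rows agree with each other. The hypothesis fits neither.

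**2. Inputs.** From the protocol: 108 participants, 4 × 27 = 108, so n = 27 per arm; significance at P<.05. Assumed: two-sided tests (sidedness is not stated), zero specific effect of every technique, independent arms, and one common mean improvement d in units of the SD of the change score. The protocol gives no SD, effect size or expected change, so a range of d is shown. A paired t test from baseline to 2 months stands in for the three-time-point repeated-measures ANOVA.

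**3. Chance that the hypothesis is confirmed on one outcome when no technique has an effect.** Power in one arm = P(T > 2.056), where T is noncentral t with 26 df and noncentrality d√27. For all four arms, raise this to the fourth power.

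| d | d√27 | one arm | all four arms |
|---|---|---|---|
| 0.4 | 2.08 | 51.7% | 7% |
| 0.5 | 2.60 | 70.6% | 25% |
| 0.6 | 3.12 | 85.1% | 52% |
| 0.75 | 3.90 | 96.3% | 86% |
| 1.0 | 5.20 | 99.9% | 99.5% |

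For example, at d = 0.75, 0.963⁴ = 0.86. The all-four probability reaches 80% at d = 0.71 and 90% at d = 0.78.

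**4. On the VAS scale.** Assume an SD of 2.0 cm and a within-person correlation ρ. The SD of change is 2.0 × √(2(1−ρ)), which is 2.0 cm at ρ = 0.5. A common fall of 1.0, 1.5 or 2.0 cm then gives d = 0.5, 0.75 or 1.0. Letting ρ run from 0.3 to 0.7, the all-four probability is 10% to 65% for a 1.0 cm fall, 62% to 99% for 1.5 cm, and 95% to over 99% for 2.0 cm.

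**5. The planned between-arm test under the same conditions.** In 20,000 simulated trials with identical arms (SD 2.0 cm, ρ = 0.5), all four within-arm tests were significant in 86% of trials at a 1.5 cm fall and 99.5% at 2.0 cm. The group-by-time test on the change from baseline to 2 months rejected in about 5%, its nominal level.

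**6. What the between-arm contrasts can detect.** The detectable standardised difference at 80% power is (z for alpha + z for power) × √(2/27):
- alpha 0.05: (1.960 + 0.842) × 0.272 = 0.76 SD.
- first Holm step if all six pairs are tested (0.05/6): (2.638 + 0.842) × 0.272 = 0.95 SD.

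Power at a true difference of 0.5 SD is 45% and 21% respectively. Non-significant pairs are therefore likely, and they would not show equivalence.

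**The case against.** The strongest reply is that the superiority question is already provided for. The protocol plans a comparison of changes among groups, a group-by-time model and a multiplicity rule, and its Conclusions speak of comparative efficacy. For that question four active arms are enough, and the lack of an untreated arm is no flaw. The hypothesis sentences stand in an abstract's Results slot and in the Discussion, and authors may expect all arms to improve while testing whether they differ. Testing change over time is a conventional companion to the interaction test.

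Most of this stands. A reader might infer that the trial has no between-arm analysis, or that its ranking will come from pre-post tests. The documents support neither: the between-arm tests are there, and nothing says the ranking rests on within-arm results. The Holm contrasts can support at least a partial ordering.

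A reader might also infer that the hypothesis is bound to be confirmed. It is not. At a common change of 0.4 SD the probability is 7%. The calculation also covers one outcome, whereas the hypothesis names pain and disability together, and the Conclusions add COG displacement.

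Nor is an observed order mostly chance. If true steps between arms are 0.2 SD (assumed), the full order is right 39% of the time, against 1 in 24 (4%) by guessing, and the truly best arm ranks first 74% of the time. Such a ranking is uncertain, but it carries information.

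The reply does not explain why the only hypotheses written down, three times over, are within-arm, or why none is attached to the tests that serve the aim.

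**Conclusion.** The concern holds as a mismatch between hypothesis and aim. The stated hypotheses are reductions within every arm; the design and aim are between-arm; the planned between-arm tests have no hypothesis attached. Confirming the hypothesis as written would not show that any technique works, because all arms share heat, exercise and natural course.

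How easily it could be confirmed without any technique effect depends on the size of the common improvement, which the protocol does not give: 25%, 86% or 99.5% on one outcome at an assumed 0.5, 0.75 or 1.0 SD of change. The right wording is therefore *could* be confirmed, not *would*.

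The between-arm tests can show that techniques differ. Without an arm that omits the manual technique, even they cannot show that any technique adds to heat and exercise. The correction is to wording, but it changes what the trial may conclude and should be made. Confidence is high for the point in this form.

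**What to change.** - **Hypothesis.** In the Abstract (Results), Primary Findings and Conclusions, state that the mean change from baseline (T0) to the 2-month follow-up (T3) in VAS and MODI differs between at least two of the four techniques. Tie this to the group-by-time model and Holm-adjusted contrasts already in Data Analysis.
- **Within-arm change.** Report it descriptively, as means with 95% CIs, with no efficacy claim.
- **Scope of conclusions.** Limit them to relative effects among the four techniques, each given with heat and exercise.
- **Superiority and ranking.** Call one technique better than another, or rank it higher, only where the Holm-adjusted contrast at the 2-month end point excludes zero. Say that non-significance is not equivalence. Rank probabilities are optional.

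**Cost.** Wording only: no new participants, data or arms. The downside is a less favourable headline claim, since four significant falls would no longer count as confirmation.

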**Conclusions:**

This protocol is designed to provide robust comparative data on manual therapy approaches for SIJ dysfunction. Findings may guide physiotherapy practice by informing evidence-based recommendations for optimal management strategies.

## Introduction

The sacroiliac joint (SIJ) is a diarthrodial synovial joint that connects the spine to the lower extremities. Although it has limited mobility, the SIJ provides essential stability and plays a significant role in pelvic biomechanics. There are two SIJs, each located between the sacrum and the ilia on either side of the body; together with the sacrococcygeal joint and the pubic symphysis, the SIJs form the pelvic girdle [1]. The primary function of the SIJ is to bear and transfer the weight of the axial skeleton to the hip bones. This weight is then distributed to the femurs when standing or to the ischial bones when seated.

SIJ dysfunction is a condition characterized by pain and reduced range of motion of the SIJ, which may present as generalized low back pain. Studies suggest that SIJ dysfunction has a prevalence rate of 15% to 30% among individuals with low back pain [2]. The SIJ is a key component of the pelvis, and SIJ dysfunction can therefore lead to functional disability [3]. The pain and decreased range of motion associated with SIJ dysfunction make daily activities difficult. Chronic SIJ dysfunction can also displace the body’s center of gravity (COG), which typically passes through the second sacral vertebra (S2); this may further affect weight distribution and lead to gait abnormalities.

Various treatments for SIJ dysfunction, including Mulligan mobilization, Maitland mobilization, and conventional physiotherapy approaches [4], aim to alleviate pain and disability in patients with SIJ dysfunction, particularly those with long-term dysfunction. Chronic issues in the sacroiliac region can result in biomechanical alterations, leading to a shift in the COG and associated functional impairments. A 2016 systematic review of SIJ dysfunction examined treatment approaches but excluded manual therapy techniques [5]. This highlights a gap in the existing literature on the role of manual therapy in managing SIJ dysfunction.

Currently, there is insufficient evidence to guide practitioners in selecting the most effective techniques for treating SIJ dysfunction. While studies have investigated the effects of Mulligan mobilization, Maitland mobilization, high-velocity thrust (HVT), and conventional physiotherapy on pain and functional disability in SIJ dysfunction, findings remain inconclusive. Available evidence is conflicting regarding which intervention is most effective, creating uncertainty among practitioners.

Although each technique is well established individually, no comparative study has been conducted to evaluate the relative efficacy of these manual therapy approaches. A comparative analysis of these techniques could provide valuable evidence to guide clinical decision-making and optimize treatment outcomes for individuals with SIJ dysfunction.

This study aims to compare the efficacy of Mulligan mobilization, Maitland mobilization, HVT, and muscle energy technique (MET) in improving pain, functional disability, and COG displacement in patients with SIJ dysfunction and to rank these approaches according to their efficacy.

## Methods

### Ethical Considerations

Following approval from the Datta Meghe Institute of Higher Education and Research Institutional Ethics Committee on April 9, 2025 (DMIHER(DU)/IEC/2025/230), 108 participants will be recruited through the Department of Musculoskeletal Physiotherapy at Ravi Nair Physiotherapy College, Sawangi (Meghe), Wardha. All participants will provide written informed consent before enrollment and will be given the opportunity to ask the researcher questions. Participants may withdraw from the study at any time. This trial is registered with Clinical Trials Registry–India (CTRI/2025/08/093085).

### Study Design

This is a prospective, 4-arm, parallel-group, randomized controlled trial to assess superiority. The study protocol was developed in accordance with the SPIRIT (Standard Protocol Items: Recommendations for Interventional Trials) guidelines. Data will be collected on pain, disability, and COG displacement. The trial will be reported in accordance with the CONSORT (Consolidated Standards of Reporting Trials) 2010 guidelines.

### Eligibility Criteria

Inclusion criteria are as follows: participants must (1) be willing to sign informed consent, (2) be diagnosed with SIJ dysfunction, (3) be aged 18 to 35 years, (4) have positive Gaenslen and Gillet tests, (5) have a symptom duration of 4 to 8 weeks, and (6) have a BMI of 18.5 to 25. Participants will be excluded if they (1) have an active infection, (2) have a cognitive disorder, (3) have osteoporosis, (4) have a history of recent surgery, (5) have posttraumatic back pain, or (6) have lumbar radiculopathy.

### Participant Recruitment

Participants who meet the inclusion criteria will be enrolled in this study. A computer-generated randomization sequence will be used to randomly allocate participants to 4 groups in a 1:1:1:1 ratio. The sequence will be generated by a supervisor (LL) who will not be involved in recruitment or treatment. The allocation sequence will be placed in sequentially numbered, opaque, sealed envelopes by the supervisor. The envelopes will be stored in a locked cabinet until they are opened by the treating therapist immediately prior to treatment. Participants will be blinded to group allocation and the specific manual therapy technique received. All interventions will be delivered in the same clinical setting with standardized session duration. Outcomes will be assessed by an independent assessor who will be blinded to treatment allocation. The treating therapist will not be involved in outcome assessment. Unblinding will not be permitted for the participants or assessor.

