### Criteria for Treatment Termination

Treatment will be terminated under specific circumstances for individual participants in each group. Treatment will be terminated for a participant (1) in group A if the participant is unable to actively participate or follow self-maintenance techniques, (2) in group B if symptoms are aggravated by passive movement, that is, if the participant experiences hyperreactivity to passive movement, (3) in group C if the participant experiences negative neurological change, feelings of fear, or excessive joint movement after HVT manipulation, or (4) in group D if the participant experiences muscle guarding or is unable to perform isometric contractions.

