### Outcomes

The primary outcomes are changes in pain and disability. The subjective experience of pain will be measured using the VAS (*r*=0.94; *P*<.001) [15]. Participants will be shown the VAS, a 10-cm scale representing levels of pain, where 0 represents no pain and 10 represents unbearable pain, and asked to indicate their current level of pain. Functional disability will be measured using the MODI (*r*=0.87; *P*<.05) [16,17], a questionnaire that provides an assessment of the effect of low back pain on daily life. The score is calculated on a scale of 0% to 100% based on responses to the questionnaire.

The secondary outcome is change in COG displacement from the baseline, measured using a force plate. This will be measured at baseline, after 3 weeks of treatment, and at the 2-month follow-up using a force plate, which will be calibrated every 6 months by a biomedical technician. The force plate will be connected to a personal computer on which COG analysis software is installed. Participants will be asked to remove their footwear, stand on the force plate with their feet positioned on the designated markings, and distribute their weight equally between both feet. Participants will be asked to stand still for 30 seconds while the force plate measures sway velocity, lift-up index on the left and right, COG alignment, movement time, and impact index.

All outcomes will be assessed before the 3-week treatment begins, after three weeks of treatment, and at follow-up 2 months after treatment ends. The primary end points will be the change in all pain and disability from baseline to the 2-month follow-up, and the secondary end point will be the change in COG displacement from baseline to the 2-month follow-up. Changes in outcomes will be compared among the 4 groups after the 2-month follow-up.

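### Participants are said to be blinded to the technique they receive, but the procedures described cannot be concealed from them, and they rate both primary outcomes

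*Protocol article*

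**What the plan says.** The protocol article, under Participant Recruitment, makes an unqualified claim: "Participants will be blinded to group allocation and the specific manual therapy technique received". It supports this with "All interventions will be delivered in the same clinical setting with standardized session duration" and adds "Unblinding will not be permitted for the participants or assessor". For outcome assessment it says "Outcomes will be assessed by an independent assessor who will be blinded to treatment allocation", and it keeps the treating therapist out of that assessment.

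The Intervention section then describes four different hands-on procedures, including, for the HVT arm, "rapid, controlled thrusts applied by the clinician to restore joint alignment". The Discussion (Primary Findings) says that Mulligan mobilization "works on the principle of sustained accessory glide with active movement". Under Criteria for Treatment Termination, one ground in the MET arm is that the participant "is unable to perform isometric contractions".

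Under Outcomes, the primary outcomes are pain and disability. For pain, participants are "asked to indicate their current level of pain" on the VAS. Disability comes from the MODI, a questionnaire. The primary end points are the changes from baseline to the 2-month follow-up.

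**The concern.** The article claims more than blinding to the hypothesis or to the name of a technique. It claims blinding to the technique itself, and its own account of the procedures does not allow that.

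The claim matters because the participant is the rater for both primary outcomes. If participants in different arms hold different expectations of what is being done to them, the difference can enter the VAS and MODI contrasts directly. Study Design describes the trial as one of superiority, and the Introduction says the techniques will be ranked by efficacy, so those contrasts are what the trial will be read for. Adjusting the pairwise tests by the Holm method controls multiplicity and does not remove bias. A reader who accepts the blinding statement would rule out a source of bias that the design leaves open.

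**Working it through.** The article attaches no power, effect-size or SD figure to this point, so there is no number to reproduce. The check sets the blinding claim beside the procedures and the outcome measurement.

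1. **What would have to be concealed.** The claim covers two things: the group, and the specific technique received.

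2. **What the participant experiences** (Intervention; Primary Findings):
   - Group A, Mulligan: 3 sets of 10 repetitions of a glide combined with the participant's active movement.
   - Group B, Maitland: graded oscillatory mobilization, 3 sets of 30 seconds.
   - Group C, HVT: rapid thrusts, supine or side-lying.
   - Group D, MET: voluntary isometric contraction at 20% intensity.

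   The procedures differ in speed, rhythm and position, and in whether the participant is active or passive. In group D the participant carries out the contraction, and in group A the movement. A technique that needs the participant's performance cannot be hidden from that participant.

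3. **How often.** 5 sessions per week × 3 weeks = 15 sessions.

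4. **What the termination rules presuppose** (Criteria for Treatment Termination). They depend on technique-specific experience or performance: fear after the thrust in group C, and ability to contract isometrically in group D. These rules assume a participant who is aware of the procedure.

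5. **What masking is described.** Two measures only: a common clinical setting and a standardized session length. Both equalize the surroundings of treatment. Neither hides what the therapist does or asks the participant to do.

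6. **Who makes the rating** (Outcomes). The participant marks the VAS, and the MODI score is computed from questionnaire responses. The independent assessor administers or collects these scores but does not generate them. Assessor blinding therefore guards against prompting and interviewer influence, but not against the participant's own expectation. The secondary outcome, COG displacement, is measured by a force plate and is less exposed.

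**Result.** Steps 2 to 5 contradict the claim of blinding to the technique received. They do not contradict a narrower claim that participants are kept unaware of technique names, of the other arms or of the hypothesis. Step 6 shows that the contradiction bears on both primary outcomes.

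**The case against.** The strongest reply is that feeling a procedure is not the same as knowing what it is called, which group it belongs to or what the alternatives are. All four arms are active and hands-on, with identical moist heat and identical exercises. There is no sham or untreated arm that a participant could recognize as inferior. A naive participant might find the two mobilizations hard to label. The article reports written informed consent, but what participants are told about the four techniques is not shown, and a condensed article commonly leaves such detail to the full protocol. The independent assessor, with the therapist excluded, also gives the VAS and MODI some protection against pressure to please the therapist.

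Most of this stands, and it limits the point. A reader might infer that the primary outcomes are in effect open-label. The documents do not support that, because awareness of one's own procedure does not imply knowledge of the comparison, and masking to group could be in place. A reader might also infer a particular inflation of false-positive findings, or a bias in favour of the thrust. Neither can be derived. The article gives no SD and no estimate of expectation effects, and since fear after HVT is one of its termination grounds, expectation could run in either direction. Nor can one say that the assessor's blinding protects only the force-plate outcome.

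The reply does not rescue the sentence as written, which names the technique received and not merely its label. It is also true that awareness of the procedure is inherent in comparing manual techniques. That is a reason to describe the design accurately; it does not make the blinding claim correct.

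**Conclusion.** The blinding statement is wrong as written with respect to the technique received. The error concerns a stated property of the design and bears on how both primary comparisons and the ranking may be interpreted. Its numerical effect is unknown: no bias is demonstrated, and its size and direction cannot be obtained from the documents.

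The conclusion rests on two premises, both from the article: that the procedures are carried out as described on conscious participants, some of whom must perform part of them, and that the VAS and MODI are participant-reported. It does not depend on what the consent form says. Blinding of the assessor is not disputed, and blinding of participants to group, technique names or hypothesis is left open. The correction is small in extent, but it should be made before results are reported.

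**What to change.** - **Blinding statement (Participant Recruitment).** Replace the sentence with one saying that the outcome assessor is blinded, that participants are aware of the procedure they receive, and that they are kept unaware of specified items. List only items that are in fact withheld, for example technique names, the content of the other arms or the study hypothesis. Bring the sentence on unblinding into line.
- **Description of results.** Describe the VAS and MODI comparisons, and any ranking based on them, as participant-reported outcomes without blinding to the procedure. State differential expectation between arms as a limitation.
- **Optional.** Add one perceived-allocation item at the 2-month follow-up, asked after the VAS and MODI are completed so that it cannot influence the primary end points. If a baseline expectation item is wanted, word it generically. Asking participants to rate each of the four techniques would disclose all the arms and undo whatever masking exists.

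**Cost.** The required changes are to text only and apply to every participant, including the 63 recruited by November 2025. The downside is a less favourable blinding statement and, if the perceived-allocation item is adopted, one extra question.
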